### 8.1.3 Exploratory objective

#### Other study parameters (if applicable)

For the analysis of the data the study parameters which are collected are gender, age, co-medication, comorbidity, vaccination status and actual (gone through) COVID-19 infections.

## 8.2 Randomisation, blinding and treatment allocation

The cohort will be filled by Amsterdam UMC (n=40), LUMC (n=40), UMCG (n=40) and Erasmus MC (n=280) with 400 participants vaccinated primarily with Janssen (n=200) or mRNA (n=200; Moderna/Pfizer). Participants will be randomised in one of the following groups, stratified by priming vaccine.

- Direct boost
- Postponed boost

Randomization will be done after obtaining written informed consent.

## SAMPLING STRATEGY

[figure not shown]

Group: PostPoned boost

[figure not shown]

### 8.3 Study procedures

All participants at day of informed consent

- Sign informed consent
- Randomization in DB or PPB group
- Fill a baseline characteristics questionnaire

**All participants at day 0:**

#### DB group

- Request to fill a COVID-19 questionnaire (online questionnaires via e-mail).
- One serum tube (8.5ml)
- One lithium heparin tube (10ml)
- Four lithium heparin tubes (4x10ml)\*
- Boost with additional vaccine

\*only in the detailed immunological assessment group

#### PPB group

- Request to fill a COVID-19 questionnaire (online questionnaires via e-mail).
- One serum tube (8.5ml)
- One lithium heparin tube (10ml)
- Four lithium heparin tubes (4x10ml)\*

\*only in the detailed immunological assessment group

**All participants DB group after 7 days (day 7)**

- Request to fill a side effects + COVID-19 questionnaire (solicited local & systemic reactions)
- One serum tube (8.5ml)
- One lithium heparin tube (10ml)
- Four lithium heparin tubes (4x10ml)\*

\*only in the detailed immunological assessment group

**All participants DB group after 28 days (day 28)**

- Request to fill a COVID-19 questionnaire
- One serum tube (4ml)

- One lithium heparin tube (10ml)
- Four lithium heparin tubes (4x10ml)\*

\*only in the detailed immunological assessment group

**All participants DB group after 180 days (day 180)**

- Request to fill a COVID-19 questionnaire
- One serum tube (4ml)
- One lithium heparin tube (10ml)
- Four lithium heparin tubes (4x10ml)\*

\*only in the detailed immunological assessment group

**All participants PPB group after 90 days (day 90) or 112 days (day 112)**

- Request to fill a COVID-19 questionnaire (online questionnaires via e-mail).
- One serum tube (8.5ml)
- One lithium heparin tube (10ml)
- Four lithium heparin tubes (4x10ml)\*
- Boost with additional vaccine

\*only in the detailed immunological assessment group

**All participants PPB group after 97 days (day 97) or 119 days (day 119)**

- Request to fill a COVID-19 questionnaire
- One serum tube (4ml)
- One lithium heparin tube (10ml)
- Four lithium heparin tubes (4x10ml)\*

\*only in the detailed immunological assessment group

**All participants PPB group after 118 days (day 118) or 140 days (day 140)**

- Request to fill a COVID-19 questionnaire
- One serum tube (4ml)
- One lithium heparin tube (10ml)
- Four lithium heparin tubes (4x10ml)\*

\*only in the detailed immunological assessment group

**All participants PPB group after 180 days (day 180) or 202 days**

- Request to fill a COVID-19 questionnaire
- One serum tube (4ml)
- One lithium heparin tube (10ml)
- Four lithium heparin tubes (4x10ml)\*

\*only in the detailed immunological assessment group

Questionnaires

Prior to the study, all participants will be given a screening questionnaire to determine whether they are eligible to participate or not. This, because a lot can have changed in the health situation in one year.

At the start of the study, a questionnaire about the basic characteristics of the HCW follows. Seven days after boost one questionnaire will be used to monitor side effects of

the vaccine. At each visit one additional questionnaire will be used to monitor occurrence and outcome of COVID-19 infection throughout the study.

#### **8.4 Withdrawal of individual subjects**

Subjects can leave the study at any time for any reason if they wish to do so without any consequences. The investigator can decide to withdraw a subject from the study for urgent medical reasons.

##### **8.4.1 Specific criteria for withdrawal (if applicable)**

Not applicable

#### **8.5 Replacement of individual subjects after withdrawal**

With the sample size calculation we have taken into account 10% lost to follow up. We will not add participants if participants drop out / quit the study.

#### **8.6 Follow-up of subjects withdrawn from treatment**

Participants who withdraw from the study will receive the same standard treatment as described in the then applicable guidelines. Already collected and distributed samples/ specimens and data will not be destroyed or deleted.

#### **8.7 Premature termination of the study**

If there is a danger to participants as a result of an additional boost, all necessary steps will be taken to safeguard the safety of the participants.

## 9. SAFETY REPORTING

### 9.1 Temporary halt for reasons of subject safety

In accordance to section 10, subsection 4, of the WMO, the sponsor will suspend the study if there is sufficient ground that continuation of the study will jeopardise subject health or safety. The sponsor will notify the accredited METC without undue delay of a temporary halt including the reason for such an action. The study will be suspended pending a further positive decision by the accredited METC. The investigator will take care that all subjects are kept informed.

### 9.2 AEs, SAEs and SUSARs

#### 9.2.1 Adverse events (Aes)

Adverse events are defined as any undesirable experience occurring to a subject during the study, whether or not considered related to the trial procedure. All adverse events reported spontaneously by the subject or observed by the investigator or his staff will be recorded. However, given the setting of a large outbreak, the registration of Aes is not feasible and will not serve the safety of the participants. Therefore, Aes will not be reported.

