#### 8.1.2 Secondary study parameters/endpoints

##### Secondary endpoints:

In addition to the primary endpoints defined above, this study will address the following secondary objectives:

1. *What is the difference in booster immunogenicity comparing a direct boost with a postponed boost?*

**Outcome:** Level of antibodies and T-cell responses 7 and 28 days post boost in DB versus PPB group.

2. *What is the breadth of the immune responses after booster vaccination?*

**Outcome:** PRNT against relevant variants in a random selection of study participants.

3. *What is the predictive value of immune responses on day 7 post boost?*

**Outcome:** Relationship between antibodies and T-cell responses on day 7 and 28 post boost.

4. *What is the difference in reactogenicity 7 days after boost comparing the Janssen and mRNA primed HCW?*

**Outcome:** Adverse events (AE) first 7 days after an additional boost between Janssen and mRNA primed HCW.

5. *Initial examination of breakthrough infections before and during study period*

**Outcome:** Database of breakthrough infections in included participants based on positive PCR, self-reported positive lateral flow test, or detection of N-specific antibodies.

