#### 9.2.2 Serious adverse events (SAEs)

A serious adverse event is any untoward medical occurrence or effect that

- results in death;
- is life threatening (at the time of the event);
- requires hospitalisation or prolongation of existing inpatients' hospitalisation;
- results in persistent or significant disability or incapacity;
- is a congenital anomaly or birth defect; or
- any other important medical event that did not result in any of the outcomes listed above due to medical or surgical intervention but could have been based upon appropriate judgement by the investigator.

An elective hospital admission will not be considered as a serious adverse event.

The registration of SAEs will be limited to SAEs that result in life threatening events, requires hospitalization or death. SAEs will be reported only from the moment of inclusion until one day after the last blood taking after 365 days. The sponsor will report the SAEs through the web portal *ToetsingOnline* to the accredited METC that

approved the protocol, within 7 days of first knowledge for SAEs that result in death or are life threatening followed by a period of maximum of 8 days to complete the initial preliminary report. All other SAEs will be reported within a period of maximum 15 days after the sponsor has first knowledge of the serious adverse events.

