### **9.2.3 Suspected unexpected serious adverse reactions (SUSARs)**

Adverse reactions are all untoward and unintended responses to an investigational product related to any dose administered.

Unexpected adverse reactions are SUSARs if the following three conditions are met:

1. the event must be serious (see chapter 9.2.2);
  2. there must be a certain degree of probability that the event is a harmful and an undesirable reaction to the medicinal product under investigation, regardless of the administered dose;
- the adverse reaction must be unexpected, that is to say, the nature and severity of the adverse reaction are not in agreement with the product information as recorded in:

- Summary of Product Characteristics (SPC) for an authorized medicinal product;
- The sponsor will report expedited the following SUSARs through the web portal ToetsingOnline to the METC :
  - SUSARs that have arisen in the clinical trial that was assessed by the METC;
  - SUSARs that have arisen in other clinical trials of the same sponsor and with the same medicinal product, and that could have consequences for the safety of the subjects involved in the clinical trial that was assessed by the METC.

The remaining SUSARs are recorded in an overview list (line-listing) that will be submitted once every half year to the METC. This line-listing provides an overview of all SUSARs from the study medicine, accompanied by a brief report highlighting the main points of concern.

The expedited reporting of SUSARs through the web portal Eudravigilance or ToetsingOnline is sufficient as notification to the competent authority.

The sponsor will report expedited all SUSARs to the competent authorities in other Member States, according to the requirements of the Member States.

The expedited reporting will occur not later than 15 days after the sponsor has first knowledge of the adverse reactions. For fatal or life threatening cases the term will be maximal 7 days for a preliminary report with another 8 days for completion of the report. Principal investigators of the participating centers in this multicenter study will report SUSARs to the coordinating investigator of this study and the coordinating investigator will be responsible for report the SUSARs as described above.

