## Procedures for reporting Adverse Events

### Solicited AEs

Participants will be asked to record local and systemic AE's for 7 days in their paper diary.

Participants are asked to fill in these AE's in a digital questionnaire 8 days after boost.

Local solicited AEs; pain, redness, warmth, swelling

Systemic solicited AEs; joint pain, fatigue, fever, chills, headache, muscle pain, nausea

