### Unsolicited AEs

All local and systemic AEs occurring 28 days following boost observed by the Investigator or reported by the participant.

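### The protocol's rules for collecting adverse events, the side-effects form in the postponed arm and SAE registration are inconsistent and need to be reconciled

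*Protocol*

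**What the plan says.** **Adverse events in general.** Section 9.2.1 opens by having all events that a participant volunteers or staff observe recorded. The same paragraph then says, citing the outbreak setting, that "the registration of Aes is not feasible and will not serve the safety of the participants. Therefore, Aes will not be reported".

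**What the endpoint and procedures need.** The fourth secondary endpoint (Summary, sections 2, 8.1.2 and 10.2) is "Adverse events (AE) first 7 days after an additional boost between Janssen and mRNA primed HCW". The procedures for reporting adverse events, after section 9.2.3, set up three streams:
- solicited reactions, kept in a paper diary for 7 days and then entered online: "Participants are asked to fill in these AE's in a digital questionnaire 8 days after boost";
- unsolicited events: "All local and systemic AEs occurring 28 days following boost observed by the Investigator or reported by the participant";
- medically attended events, asked about at study visits up to 3 months after the boost.

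Section 9.5 adds weekly investigator meetings at which types of adverse event are discussed.

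**Visit lists (section 8.3).** The direct-boost day-7 visit has "Request to fill a side effects + COVID-19 questionnaire (solicited local & systemic reactions)". The postponed-boost counterpart, "All participants PPB group after 97 days (day 97) or 119 days (day 119)", lists a COVID-19 questionnaire and blood tubes only.

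**Serious events.** Section 9.2.2 defines six categories of seriousness and then says: "The registration of SAEs will be limited to SAEs that result in life threatening events, requires hospitalization or death". Section 9.2.3 makes it a condition of a SUSAR that "the event must be serious (see chapter 9.2.2)". Section 9.3 requires a yearly list of all suspected serious adverse reactions.

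**The concern.** Sites need one rule for each kind of safety data, and here they have two. A site that applies the end of the first paragraph of section 9.2.1 has grounds not to register events that the later procedures ask it to collect. A site that works from the postponed-arm visit list has no prompt to send the side-effects form. A site that applies the SAE limit need not register some events that the SUSAR and annual-report rules depend on.

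At stake are the completeness of one named secondary endpoint, the comparability of reactogenicity data between the two randomised arms, and whether the SUSAR and annual-report duties can be carried out as written. The primary endpoint is not touched.

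**Working it through.** The protocol gives no power or precision figure for reactogenicity, so there is none to reproduce. The check sets texts side by side and adds a little arithmetic.

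**1. Adverse-event rule**

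| Place | Effect |
|---|---|
| 9.2.1, first part | volunteered or observed events are recorded |
| 9.2.1, end of same paragraph | registration rejected; events not reported |
| Solicited AEs | 7-day diary plus online form |
| Unsolicited AEs | 28 days after boost |
| Medically attended AEs | up to 3 months after boost |
| 9.5 | investigators discuss event types weekly |
| Secondary endpoint 4 | 7-day events compared by priming vaccine |

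Reading the end of 9.2.1 as being only about reporting to the ethics committee would settle the last clause. It would not settle the clause before it, which is about registration.

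**2. Side-effects form**

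- Section 8.3 boosts the postponed arm on day 90 or day 112.
- 90 + 7 = 97 and 112 + 7 = 119, so the day 97/119 visit is the exact counterpart of direct-boost day 7.
- No side-effects form appears there, nor at any other postponed-arm visit in section 8.3.
- Three general texts ask for the form after the boost with no arm restriction: Randomisation/Blinding in section 3, Questionnaires at the end of section 8.3, and Solicited AEs.
- Completion day: day 7 in the direct-boost list and under Questionnaires; day 8 in section 3 and under Solicited AEs. The protocol does not say whether the 7 diary days start on the day of the boost. If they start the day after, a form completed at the day-7 visit is completed before the last diary day is over.

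Size if sites followed the visit list alone: section 3 (Study groups) plans 200 per priming cohort, 100 of them in each boost arm. Without the postponed arm, the comparison of priming vaccines falls from 200 vs 200 to 100 vs 100. The standard error of a difference between two groups of n each is proportional to √(2/n), so the ratio is √(200/100) = √2 = 1.41.

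The protocol gives no event rate, so the rates p below are assumptions. The 95% half-width is 1.96 × √(2p(1 − p)/n):

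| Assumed rate p | n = 200 per group | n = 100 per group |
|---|---|---|
| 10% | 5.9 points | 8.3 points |
| 30% | 9.0 points | 12.7 points |
| 50% | 9.8 points | 13.9 points |

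These use planned numbers. Equal proportional loss to follow-up leaves the ratio at 1.41.

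**3. Serious events**

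| Category in 9.2.2 | Registered? |
|---|---|
| Death | yes |
| Life-threatening | yes |
| Hospitalisation | yes |
| Disability or incapacity | no |
| Congenital anomaly or birth defect | no |
| Other important medical event | no |

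Three of six are registered. Section 9.2.3 refers to 9.2.2 for seriousness without repeating the limit, and section 9.3 sets no category limit.

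**The case against.** The strongest reply is that specific text should prevail over one general sentence. The recording rule in section 9.2.1 is about volunteered or observed events, whereas the endpoint has its own diary and questionnaire, described in several places. In a safety-reporting chapter, reporting may mean reporting to the ethics committee. This stands to a large extent. A reader might infer that section 9.2.1 leaves the endpoint with no data, and the protocol does not support that. What remains is the conflict inside the paragraph and with the unsolicited and medically attended streams.

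On the postponed arm, a reader might infer that its 200 participants are not to be asked about side effects. The three general texts show otherwise: an item is missing from a list. Even without that arm, both priming groups would be present in the direct-boost arm, so the comparison would lose precision but could still be made.

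On serious events, a reader might infer that a disabling reaction without hospitalisation could never be assessed as a SUSAR. That is too strong. The SUSAR rule itself is not narrowed, site investigators report SUSARs to the coordinating investigator, and such a reaction could surface as an unsolicited event within 28 days or a medically attended one within 3 months. A narrower registration rule may also be deliberate, since section 12.2 classes the study as negligible risk. Even so, those routes are time-limited, and section 9.2.1 makes them uncertain.

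The day 7 versus day 8 difference is minor, and would not need raising on its own.

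**Conclusion.** The concern holds as a set of inconsistencies in operative text:

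- Section 9.2.1 contradicts itself and the later collection procedures.
- The postponed-arm visit list omits a form that the general text requires, and the form has two completion days.
- SAE registration covers three of six categories, while the SUSAR and annual-report rules use seriousness without that limit.

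The factor of 1.41 is conditional: it applies only if sites follow the visit list and disregard the general text. The half-widths rest on assumed event rates as well. The document does not show a plan to collect no reactogenicity data, to skip one arm, or to shut any category of serious reaction out of SUSAR assessment. The corrections should be made because sites cannot follow all the rules as written and the cost is small. Which safety-registration rule is right is for the sponsor to decide.

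**What to change.** 1. Reconcile section 9.2.1 with the solicited, unsolicited and medically attended procedures and with secondary endpoint 4, so that collection of the events the endpoint needs is beyond doubt. If the limit on reporting is meant only for the ethics committee, say so.
2. Add the side-effects questionnaire to the postponed-boost visit on day 97 or 119 in section 8.3. Give one completion day, the same in both arms and in every place it is mentioned, that covers the full 7-day diary.
3. Reconcile the SAE registration limit in section 9.2.2 with sections 9.2.3 and 9.3, so that the SUSAR and annual-report duties can be carried out. If the limit is intended, state how events in the other three categories reach those two processes.

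The cost is protocol wording plus an existing questionnaire named in one more visit list. Items 1 and 2 change neither the design nor the sample size; any extra registration work under item 3 depends on how the sponsor resolves it.

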#### Adverse Reaction (AR)

An untoward and unintended response in a participant to an investigational medicinal product which is related to any dose administered to that participant. The phrase "response to an investigational medicinal product" means that a causal relationship between a trial medication and an AE is at least a reasonable possibility, i.e. the relationship cannot be ruled out.

All cases judged by either the reporting medically qualified professional or the Sponsor as having a reasonable suspected causal relationship to the trial medication qualify as adverse reactions.

#### 9.2.2 Serious adverse events (SAEs)

A serious adverse event is any untoward medical occurrence or effect that

- results in death;
- is life threatening (at the time of the event);
- requires hospitalisation or prolongation of existing inpatients' hospitalisation;
- results in persistent or significant disability or incapacity;
- is a congenital anomaly or birth defect; or
- any other important medical event that did not result in any of the outcomes listed above due to medical or surgical intervention but could have been based upon appropriate judgement by the investigator.

An elective hospital admission will not be considered as a serious adverse event.

The registration of SAEs will be limited to SAEs that result in life threatening events, requires hospitalization or death. SAEs will be reported only from the moment of inclusion until one day after the last blood taking after 365 days. The sponsor will report the SAEs through the web portal *ToetsingOnline* to the accredited METC that

approved the protocol, within 7 days of first knowledge for SAEs that result in death or are life threatening followed by a period of maximum of 8 days to complete the initial preliminary report. All other SAEs will be reported within a period of maximum 15 days after the sponsor has first knowledge of the serious adverse events.

### **9.2.3 Suspected unexpected serious adverse reactions (SUSARs)**

Adverse reactions are all untoward and unintended responses to an investigational product related to any dose administered.

Unexpected adverse reactions are SUSARs if the following three conditions are met:

1. the event must be serious (see chapter 9.2.2);
  2. there must be a certain degree of probability that the event is a harmful and an undesirable reaction to the medicinal product under investigation, regardless of the administered dose;
- the adverse reaction must be unexpected, that is to say, the nature and severity of the adverse reaction are not in agreement with the product information as recorded in:

- Summary of Product Characteristics (SPC) for an authorized medicinal product;
- The sponsor will report expedited the following SUSARs through the web portal ToetsingOnline to the METC :
  - SUSARs that have arisen in the clinical trial that was assessed by the METC;
  - SUSARs that have arisen in other clinical trials of the same sponsor and with the same medicinal product, and that could have consequences for the safety of the subjects involved in the clinical trial that was assessed by the METC.

The remaining SUSARs are recorded in an overview list (line-listing) that will be submitted once every half year to the METC. This line-listing provides an overview of all SUSARs from the study medicine, accompanied by a brief report highlighting the main points of concern.

The expedited reporting of SUSARs through the web portal Eudravigilance or ToetsingOnline is sufficient as notification to the competent authority.

The sponsor will report expedited all SUSARs to the competent authorities in other Member States, according to the requirements of the Member States.

The expedited reporting will occur not later than 15 days after the sponsor has first knowledge of the adverse reactions. For fatal or life threatening cases the term will be maximal 7 days for a preliminary report with another 8 days for completion of the report. Principal investigators of the participating centers in this multicenter study will report SUSARs to the coordinating investigator of this study and the coordinating investigator will be responsible for report the SUSARs as described above.

